### Study discontinuation

A participant will be withdrawn from the primiparous cohort if she does not wear the accelerometer at either 2–3 or 5–6 weeks AND does not complete the 8-week study visit.

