## Methods and analysis

### Study overview

This National Institutes of Health (NIH)-funded Program Project, ‘Bridging physical and cultural determinants of postpartum pelvic floor support and symptoms following vaginal delivery’ (abbreviated as *M*otherhood *A*nd *P*elvic health (MAP)), encompasses a prospective cohort study and a qualitative study and will enrol ∼1530 nulliparous women during the third trimester. After excluding women who subsequently deliver by caesarean section, deliver preterm (<37 weeks gestation), are pregnant at 1 year postpartum and after accounting for study withdrawals, we will evaluate the remaining estimated 585 women at 1 year. These women make up the primiparous cohort from which participants are drawn to meet the objectives of the Program. We will measure:
Pelvic floor support and symptoms at the third trimester, and at 8 weeks and 1 year postpartum;Antepartum predictors in the third trimester;Delivery risk factors following vaginal birth;Physical activity predictors via accelerometry at 2–3 and 5–6 weeks and 6 months postpartum;IAP, abdominal muscle endurance and waist circumference 8 weeks and 1 year postpartum; andMuscular fitness and body composition 1 year postpartum.

We chose to define the acute postpartum recovery period as 8 weeks both because of the biological plausibility noted above and because in the USA, 6–10 weeks coincides with the postpartum clinical assessment, aiding the feasibility of our study, and many working women would have returned to work by this time point.

Thirty Euro-American and 30 Mexican-American participants will be purposefully selected for qualitative interviews following the 8-week and 1-year visits. Women will be offered participation in a Pregnancy and Pelvic Floor Outcomes Registry, to be established with this study population.

This study is registered in clinicaltrials.gov (NCT02512016).

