### Study aims and adequacy of sample size for quantitative projects

The aims for the quantitative projects, as well as additional information related to sample size calculations where relevant, are summarised in table 2.

**Table 2 BMJOPEN2016014252TB2:** Quantitative study aims, hypotheses and sample size considerations

Aim: to determine…	Hypotheses	Two-sided significance level	Minimal detectable OR
Whether IAP measured at 8 weeks postpartum during (a) lifting and (b) abdominal muscle endurance testing predicts pelvic floor support and symptoms 1 year postpartum.	(a) Higher IAP at 8 weeks postpartum during (a) lifting and (b) abdominal muscle endurance testing predicts worse pelvic floor support 1 year postpartum.(b) Higher IAP at 8 weeks postpartum during (a) lifting and (b) abdominal muscle endurance testing predicts greater pelvic floor symptoms 1 year postpartum.*	0.025	1.78
Whether measures of muscular fitness modify the effect of IAP during lifting on pelvic floor support at 1 year postpartum.	Women with high IAP during lifting 1 year postpartum who also demonstrate lower abdominal muscle endurance, less pelvic floor muscle strength or less grip strength 1 year postpartum will have higher odds of worse pelvic floor support at 1 year postpartum than women with high IAP but greater muscular fitness, whereas women demonstrating low IAP will have more similar odds of worse pelvic floor support regardless of fitness.†	0.017	1.82
Whether MVPA in the early postpartum period predicts pelvic floor support and symptoms 1 year postpartum.	(a) Greater daily average MVPA in the early postpartum period, measured using accelerometry at 2–3 and 5–6 weeks postpartum, predicts worse pelvic floor support 1 year postpartum.(b) Greater daily average MVPA in the early postpartum period, measured using accelerometry at 2–3 and 5–6 weeks postpartum, predicts greater symptoms 1 year postpartum.	0.05	1.70
Whether sedentary time during the later postpartum period, independent of MVPA, predicts pelvic floor support 1 year postpartum.	Greater daily average sedentary time measured using accelerometry for 7 days at 6 months postpartum is associated with worse pelvic floor support, independent of MVPA measured during the same time period.	0.05	1.70

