#### Quantitative data

The study population will consist of primiparous women who delivered vaginally and were followed longitudinally for 1 year. We will perform descriptive statistics, stratified by ethnicity, to characterise the population and will characterise the trajectories of key variables by plotting longitudinal patterns at the third trimester, and at 8 weeks and 1 year postpartum.

In this cohort study, we cannot remove prevalent cases as it is not feasible to measure pelvic floor support in this large population before pregnancy, though cases of MVD≥0 are rare in nulliparas.^97^ Since we cannot estimate true risk ratios, we will calculate the prevalence ratio for each outcome at 1 year postpartum based on each predictor, as well as model prevalence ratios using modified generalised linear models, such as logistic regression with variance correction by GEE.^98^

Analyses of dichotomous outcomes will begin with a univariate analysis of prevalence ratios and CIs for the primary predictor and potential confounders. Further modelling by multivariable modified logistic regression will adjust potential confounders based on a directed acyclic graph.^99^
^100^ We will avoid adjusting for variables downstream of a predictor in the causal path.^99^ Effect modification will be considered when cell sizes permit. Models will be checked for adequacy of the model, multicollinearity, influential observations, etc, using standard regression diagnostics. We do not anticipate time-dependent confounders since each hypothesis addresses a specific time relative to delivery. In the final analysis, missing values will be imputed as needed using sequential regression multiple imputation (ICE in Stata or IVEWARE with SAS).^101^

Nominal p values and 95% CIs will be reported. All tests will be two-sided, at the conventional 5% significance level, except as noted. When there are multiple tests to be performed simultaneously, for example, several scenarios or several predictors to be tested in separate models, we will use a proper multiple test correction to adjust for the inflation of type I error. Analysis will be performed in SAS, Stata or R.

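### The withdrawal rule removes women from the whole cohort for missing early data, although four of the nine Table 2 aims need none

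*Protocol article*

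**What the plan says.** The rule stands in the protocol article under Study discontinuation. A woman is "withdrawn from the primiparous cohort if she does not wear the accelerometer at either 2–3 or 5–6 weeks AND does not complete" the 8-week visit. Both failures are required.

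The Study overview gives that cohort its role: "These women make up the primiparous cohort from which participants are drawn to meet the objectives of the Program". Withdrawal from it is therefore withdrawal from every quantitative aim.

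Table 2 lists nine quantitative aims. Some depend on early measurements, for example "Whether IAP measured at 8 weeks postpartum during (a) lifting and (b) abdominal muscle endurance testing predicts pelvic floor support and symptoms 1 year postpartum" and "Whether MVPA in the early postpartum period predicts pelvic floor support and symptoms 1 year postpartum". Others do not. The effect-modification hypothesis concerns "Women with high IAP during lifting 1 year postpartum who also demonstrate lower abdominal muscle endurance", with fitness also measured at 1 year.

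Under Quantitative data, the article states that "missing values will be imputed as needed using sequential regression multiple imputation". It gives no reason for the withdrawal rule and does not limit the rule to the aims that use early data.

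**The concern.** A woman who meets the rule lacks the early predictors. For the aims built on those predictors, leaving her out costs little. For an aim whose predictor is measured at 6 months or 1 year, and whose outcome is measured at 1 year, nothing essential is missing at the time she is withdrawn. Ending her follow-up then creates missing data that need not exist.

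The rule also fits poorly with two other parts of the article. Primary study limitations names high withdrawal as a threat to the integrity of a cohort. Participants lets women with a stillbirth or poor neonatal outcome continue if they prefer. Such a woman could miss the first 8 weeks and then be withdrawn by rule despite that preference.

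At stake are some lost observations in four aims and a possible selection effect, if missing early contact is related to activity, fitness or pelvic floor outcome.

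**Working it through.** **1. Which aims need data from the first 8 weeks (Table 2, in order)**

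| Aim | Predictor timing | Early data needed |
|---|---|---|
| 1. Intra-abdominal pressure (IAP) | 8 weeks | yes |
| 2. Fitness as modifier of lifting IAP | 1 year | no |
| 3. Early moderate-to-vigorous activity (MVPA) | 2–3 and 5–6 weeks | yes |
| 4. Sedentary time, independent of MVPA | 6 months, both | no |
| 5. Early MVPA by high-risk delivery (exploratory) | 2–3 and 5–6 weeks | yes |
| 6. Grip strength and endurance, adjusted for pelvic floor muscle strength | 1 year | no |
| 7. Abdominal endurance | 8 weeks | yes |
| 8. Habitus | 1 year | no |
| 9. Waist circumference | 8 weeks | yes |

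All outcomes are at 1 year. Four of nine aims (2, 4, 6, 8) need no predictor from the first 8 weeks.

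**2. The plan's own sample size**

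Inputs from the sample size section: P = 0.15, R² = 0.5, power 0.90, two-sided α. For logistic regression with a continuous covariate (Hsieh):

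N = (z(1−α/2) + z(0.90))² / [P(1−P) × (ln OR)² × (1−R²)]

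- α = 0.05, OR 1.70: N = 585.4
- α = 0.025, OR 1.78: N = 585.6
- α = 0.017, OR 1.82: N = 588.6

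The stated 585 is reproduced. Power at 585 is 0.900, 0.900 and 0.898. The Study overview reaches 585 after allowing for withdrawals, so the rule does not undermine this figure.

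**3. Possible gain from keeping the women**

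The share w of otherwise evaluable women whom the rule removes is not given. Assume 1% to 10%. Then N = 585/(1−w), and power = Φ(ln OR × √(N × P(1−P) × (1−R²)) − z(1−α/2)).

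| w | N | Power, α 0.05, OR 1.70 | Power, α 0.025, OR 1.78 | Power, α 0.017, OR 1.82 |
|---|---|---|---|---|
| 1% | 591 | 0.903 | 0.903 | 0.901 |
| 2% | 597 | 0.905 | 0.906 | 0.904 |
| 5% | 616 | 0.914 | 0.915 | 0.914 |
| 10% | 650 | 0.927 | 0.929 | 0.929 |

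**4. Possible selection effect (assumed rates)**

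If removal has probability r, doubled among exposed women with the outcome, the observed odds ratio is the true one times [(1−2r)(1−r)]/(1−r)² = (1−2r)/(1−r).

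- r = 5%: 0.90/0.95 = 0.95
- r = 10%: 0.80/0.90 = 0.89

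If removal depends on neither exposure nor outcome, the factor is 1.

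**5. The wording of the accelerometer condition**

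- Neither wear period completed: a withdrawn woman has no early accelerometry.
- At least one wear period missed: a woman with one usable early week who also misses the 8-week visit is withdrawn, which costs data in aims 3 and 5 too.

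The two readings give different cohorts.

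**The case against.** The strongest reply is that the rule is narrow. A woman who completes the 8-week visit stays in whatever her accelerometry. On the more natural reading, only women with no accelerometer wear in either early period and no 8-week visit are withdrawn. Many of them may be lost anyway, and nothing in the article shows that they would attend later. This stands, and it limits the expected yield.

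It is also fair that such women would not be complete cases. Table 1 collects postpartum wound and postpartum practices only at the 8-week visit, so these would be missing if the causal diagram calls for them. They would, however, be missing covariates and not a missing predictor or outcome.

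Three stronger readings are tempting, and the documents do not support them:

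- A reader might take 585 of about 1530 (38%) as a sign of how much the rule costs. That gap also covers caesarean delivery, preterm delivery and pregnancy at 1 year. If one assumes 20–35%, 5–10% and 3–10% for these (none is in the article), 806 to 1128 women remain, and 27% to 48% of them are lost for all other reasons together. The rule's share of that loss cannot be separated and could be close to zero.
- A reader might infer that the results will be biased. No size or direction follows from the documents.
- A reader might argue that multiple imputation makes the rule unnecessary, or that the analysis population, "The study population will consist of primiparous women who delivered vaginally and were followed longitudinally for 1 year", must be redefined with weights. Imputation is not what rescues the four later aims, since they need no early predictor, and it adds little where the whole early exposure is missing. The population sentence concerns everyone lost before 1 year and is a separate matter.

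**Conclusion.** The point holds in a limited form. The rule withdraws women from all aims for lack of data that aims 2, 4, 6 and 8 do not use. It therefore causes avoidable loss of usable data, and possibly selection, in those four aims. This follows from the text and the count in Table 2 and needs no outside figure.

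The size cannot be derived from the documents. Under the assumed 1% to 10%, the gain is 6 to 65 women, and power rises from about 0.90 to at most 0.93. The true effect may be smaller still. There is no sample size error. The ambiguity in the accelerometer condition is real and affects only women who also miss the 8-week visit. Overall this is a cheap improvement, not a threat to the study's main conclusions.

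**What to change.** Replace withdrawal from the cohort by exclusion per aim:

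- Keep these women in follow-up unless they choose to leave.
- Invite them to the 6-month accelerometry and the 1-year visit.
- Analyse them in each aim for which they have the predictor and the outcome.
- Impute covariates collected only at 8 weeks under the multiple imputation already planned.
- State whether the accelerometer condition means missing both early wear periods or at least one.

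The cost is a change of wording plus some further contacts and 1-year visits for women already enrolled. The yield will be low if most of them are lost in any case.

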### Data analysis

Requirements for reporting as outlined by the STROBE^95^ guidelines will be followed for projects 1 and 2 and by CORE_Q^96^ or equivalent for project 3.

#### Quantitative data

The study population will consist of primiparous women who delivered vaginally and were followed longitudinally for 1 year. We will perform descriptive statistics, stratified by ethnicity, to characterise the population and will characterise the trajectories of key variables by plotting longitudinal patterns at the third trimester, and at 8 weeks and 1 year postpartum.

In this cohort study, we cannot remove prevalent cases as it is not feasible to measure pelvic floor support in this large population before pregnancy, though cases of MVD≥0 are rare in nulliparas.^97^ Since we cannot estimate true risk ratios, we will calculate the prevalence ratio for each outcome at 1 year postpartum based on each predictor, as well as model prevalence ratios using modified generalised linear models, such as logistic regression with variance correction by GEE.^98^

Analyses of dichotomous outcomes will begin with a univariate analysis of prevalence ratios and CIs for the primary predictor and potential confounders. Further modelling by multivariable modified logistic regression will adjust potential confounders based on a directed acyclic graph.^99^
^100^ We will avoid adjusting for variables downstream of a predictor in the causal path.^99^ Effect modification will be considered when cell sizes permit. Models will be checked for adequacy of the model, multicollinearity, influential observations, etc, using standard regression diagnostics. We do not anticipate time-dependent confounders since each hypothesis addresses a specific time relative to delivery. In the final analysis, missing values will be imputed as needed using sequential regression multiple imputation (ICE in Stata or IVEWARE with SAS).^101^

Nominal p values and 95% CIs will be reported. All tests will be two-sided, at the conventional 5% significance level, except as noted. When there are multiple tests to be performed simultaneously, for example, several scenarios or several predictors to be tested in separate models, we will use a proper multiple test correction to adjust for the inflation of type I error. Analysis will be performed in SAS, Stata or R.

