Whether the presence of a high-risk delivery variable (forceps, prolonged second stage of labour, shoulder dystocia, anal sphincter laceration) modifies the association between MVPA in the early postpartum period on pelvic floor support and symptoms at 1 year (exploratory aim).	(a) The prevalence risk of worse pelvic floor support at 1 year will be higher for women with greater MVPA in the early postpartum period, higher in women with a high-risk delivery variable; and even higher for women with both.(b) The prevalence risk of greater pelvic floor symptoms at 1 year will be higher for women with greater MVPA in the early postpartum period, higher in women with a high-risk delivery variable; and even higher for women with both.	0.05	1.70
Whether each of grip strength and abdominal muscle endurance is associated with pelvic floor support and symptoms, independent of PFM, all measured at 1 year.	(a) Greater grip strength and greater abdominal muscle endurance are each associated with better pelvic floor support, adjusted for PFM strength.(b) Greater grip strength and greater abdominal muscle endurance are each associated with fewer symptoms, adjusted for PFM strength.*	0.025	1.78
Whether abdominal muscle endurance measured at 8 weeks predicts pelvic floor support and symptoms at 1 year.	(a) Greater abdominal muscle endurance at 8 weeks predicts better pelvic floor support 1 year postpartum.(b) Greater abdominal muscle endurance at 8 weeks predicts fewer symptoms 1 year postpartum.	0.05	1.70
The components of habitus, measured at 1 year that are associated with poor pelvic floor support and symptoms at 1 year.	(a) At 1 year postpartum, greater adiposity, as per cent body fat, and body mass index are associated with worse pelvic floor support.(b) At 1 year postpartum, greater adiposity, as per cent body fat, and body mass index are associated with greater symptoms.	0.05	1.70
Whether waist circumference at 8 weeks postpartum predicts pelvic floor support and symptoms at 1 year.	(a) Greater waist circumference at 8 weeks postpartum predicts worse pelvic floor support 1 year postpartum(b) Greater waist circumference at 8 weeks postpartum predicts greater pelvic floor symptoms 1 year postpartum.	0.05	1.70

*We use an adjusted two-sided significance level of 0.05/2=0.025, reflecting two hypothesis tests from two independent.

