†We use an adjusted two-sided significance level of 0.017 to accommodate three separate binomial regression models for statistical interaction terms between each test of muscular fitness and IAP.

IAP, intra-abdominal pressure; MVPA, moderate-to-vigorous physical activity; PFM, pelvic floor muscle strength.

We base our sample size estimate on the proportion of women expected to demonstrate pelvic floor support at or below the hymen (ie, MVD≥0 cm indicating worse support). (Based on pilot data, a higher proportion of women are expected to meet the criteria for symptom burden, our second primary outcome.) Of 10 studies identified at the onset of this research that use the POP-Q to assess vaginal support during the first postpartum year, 7 measured support 6–12 months postpartum^20^
^27^
^29^
^87–90^ (total n=1215); and 4 at 6 weeks to 6 months postpartum^21^
^22^
^28^
^91^ (total n=671). The mean anterior vaginal wall support was always worse (more positive) than the mean posterior vaginal wall or mean apical support. The distribution of stage in studies providing this ranged from 0% to 30%, 26% to 65%, 28% to 59%, and from 0% to 5% for stages I, II and III, respectively.^20–22^ The proportion of women with MVD≥0 ranged from 0% to 41%.^20^
^22^
^28^
^87^
^88^
^90^ In a pilot study of Utah women, similar to our expected population (unpublished), 18% had MVD≥0 at 1 year postpartum. We elected to conservatively estimate the proportion of women with MVD≥0 as 15%.

Sample size determinations were performed using PASS 2008. Consistent with Dunnett and Goldsmith,^92^ we did not adjust for multiplicity based on our two primary outcomes, as the inference related to the study aim does not require the simultaneous examination of the two comparisons.

Our predictors are continuous variables. We consider women at the mean for a given predictor as ‘low risk’ and those at the mean plus 1SD as ‘high risk’. Assuming that the frequency of MVD≥0 is 15% in the low-risk group and R^2^ of the predictor regressed on other predictors is 0.5, a sample size of 585 women at 1 year follow-up provides 90% power to detect the minimal OR shown in table 2 for women whose predictor value is 1SD higher than other women whose value is at the mean. (R^2^ is likely to be lower; if so, this sample size provides 90% power to detect even lower odds).

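### The model named for prevalence ratios is described only by a variance correction, which cannot produce a prevalence ratio, and the scale of the effect-modification tests shifts between sections

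*Protocol article*

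**What the plan says.** In the protocol article, under Data analysis, Quantitative data, the effect measure is clear: "we will calculate the prevalence ratio for each outcome at 1 year postpartum based on each predictor". For modelling, the same sentence says the authors will "model prevalence ratios using modified generalised linear models, such as logistic regression with variance correction by GEE". For the adjusted analysis it says: "Further modelling by multivariable modified logistic regression will adjust potential confounders based on a directed acyclic graph". The word 'modified' appears in both modelling statements, but the variance correction is the only modification described.

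The scale used for effect modification varies by place:

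- **Table 2, muscular fitness by intra-abdominal pressure (IAP) aim:** the less fit women with high IAP "will have higher odds of worse pelvic floor support at 1 year postpartum than women with high IAP but greater muscular fitness". The detectable effect is given as an OR of 1.82 at a two-sided level of 0.017.
- **Table 2, second footnote, same tests:** "three separate binomial regression models for statistical interaction terms between each test of muscular fitness and IAP". No link function is given.
- **Table 2, exploratory aim on high-risk delivery by moderate-to-vigorous physical activity (MVPA):** "The prevalence risk of worse pelvic floor support at 1 year will be higher for women with greater MVPA in the early postpartum period", higher with a high-risk delivery, and higher still with both.
- **Quantitative data section:** prevalence ratios, with no scale fixed for interaction terms.

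**The concern.** A GEE or sandwich correction alters standard errors and leaves point estimates alone. The exponentiated coefficient of a logit-link model is an OR whatever variance is attached to it. An analyst who followed the section literally, and labelled the result a PR, would overstate every association with prevalence above 1. The overstatement grows with outcome frequency, so it would be worst for the symptom outcome, which the article expects to be the more common of its two primary outcomes.

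Effect modification depends on scale. If two factors both affect the outcome, absence of interaction in odds implies some interaction in prevalence ratios and in prevalence differences. A plan that words one hypothesis in odds, another in risk, and the analysis in PRs leaves the result of two aims open to a choice made after the data are seen. One of those aims, fitness by IAP, is not labelled exploratory and has its own significance level.

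**Working it through.** **Inputs.** From the sample size section and Table 2: N = 585; 15% with worse support in the low-risk group; R² = 0.5; 90% power; two-sided levels 0.05, 0.025 and 0.017; minimal detectable ORs 1.70, 1.78 and 1.82 per SD. The symptom prevalence is given only as higher than that for support, so 30% to 50% is an assumption here.

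**Step 1: the plan's own figures.** For logistic regression with a continuous predictor, OR = exp[(z(1−α/2) + z(0.90)) / √(N·P·(1−P)·(1−R²))]. The root is √(585 × 0.15 × 0.85 × 0.5) = √37.29 = 6.107. The results are 1.700, 1.780 and 1.823, so Table 2 reproduces. The power calculation is on the OR scale throughout.

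**Step 2: OR to PR.** PR = OR / (1 − p0 + p0·OR).

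| Baseline prevalence p0 | PR when OR = 1.70 |
|---|---|
| 15% (planned, support) | 1.70/1.105 = 1.54 |
| 30% (assumed, symptoms) | 1.70/1.21 = 1.40 |
| 40% (assumed, symptoms) | 1.70/1.28 = 1.33 |
| 50% (assumed, symptoms) | 1.70/1.35 = 1.26 |

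At 15%, OR 1.78 is PR 1.59 and OR 1.82 is PR 1.62.

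**Step 3: what a variance correction does.** Two simulated data sets of 200,000 records each had a binary exposure, one binary covariate and a log-linear truth.

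| Estimator (exponentiated) | True PR 1.54, base risk 15% | True PR 1.40, base risk 40% |
|---|---|---|
| Logistic, model-based variance | 1.75 | 2.10 |
| Logistic, robust variance | 1.75 | 2.10 |
| Poisson, log link, robust variance | 1.549 | 1.396 |
| Logistic, cases duplicated as non-cases, cluster-robust variance | 1.548 | 1.396 |
| Logistic, standardised predictions | 1.549 | 1.396 |

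The variance correction does not move the estimate. Three other modifications recover the PR, and two of them are forms of logistic regression.

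**Step 4: interaction scale.** Take p00 = 15% and let each factor alone have OR 1.70. The baseline odds are 0.15/0.85 = 0.1765, and each factor alone gives odds 0.30, or 23.1%.

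- *No interaction in odds:* joint odds 0.51, so p11 = 33.8%. The ratio of PRs is 0.3377 × 0.15 / 0.2308² = 0.951 (negative). The additive contrast is 33.8 − 2 × 23.1 + 15.0 = +2.6 points (positive).
- *No interaction in PRs:* p11 = 0.2308²/0.15 = 35.5%. The ratio of ORs is 1.079.
- With both ORs at 1.82 the three figures are 0.936, +3.3 points and 1.112.

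A joint prevalence between 33.8% and 35.5% is therefore a positive interaction in odds and a negative one in PRs. The pattern 15.0%, 23.1%, 23.1%, 33.8% also satisfies the exploratory hypothesis as worded, although it contains no odds-scale interaction. Without a scale, that hypothesis cannot separate effect modification from two independent effects.

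This gap needs both factors to have an effect. If fitness had none at low IAP, the no-interaction value of p11 would be the same on every scale.

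**The case against.** The strongest reply is that the text does not describe ordinary logistic regression. It says 'modified' twice and offers logistic regression only as an example. Each outcome is analysed once per woman at 1 year, so a plain logistic model would have no repeated records calling for GEE. A robust variance is what duplicated records or a working Poisson model require. The stated purpose is to model PRs, and a source is cited that is not available here. A condensed article may also leave the link or data expansion to the full protocol or analysis plan.

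Much of this stands. A reader might infer that the trial will report ORs as PRs, for example a 33% excess reported as 70% at 40% prevalence. The document does not support that: nothing in it says an exponentiated logit coefficient will be presented as a PR, and 40% is not its figure. What remains is narrower. The article chose to name the method, and the one modification it spells out is the one that cannot yield the estimand.

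On interaction, the reply is that binomial regression could mean log-binomial, that the risk wording of the exploratory aim fits PRs, and that only the odds hypothesis is out of line. A ratio of ORs of 1.079 is also small beside a detectable OR of 1.82, and effect modification is to be examined only where cell sizes allow. These points limit the consequence. They do not settle which scale applies to the fitness by IAP tests, which are hypothesised in odds, modelled with no stated link and placed in a PR framework.

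**Conclusion.** The point holds in limited form. The estimand is a PR; the method as worded describes a variance correction to logistic regression and omits the step that turns its output into a PR. If the wording were followed literally, OR 1.70 would stand in for PR 1.54 at 15% prevalence and for PR 1.40 to 1.26 at 30% to 50%. The second range rests on an assumed symptom prevalence.

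The interaction scale is unreconciled in the text. The effect is modest at 15% prevalence, yet it can reverse the sign of an interaction. The figures assume that both factors act at OR 1.70, and the gap narrows if either effect is weak.

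A reader might also infer that the power statement is undermined. It is not: the Table 2 ORs reproduce and N = 585 does not change. This is a correction to make before analysis, not a flaw that threatens the study.

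**What to change.** 1. In the Quantitative data section, replace the logistic example with a model that yields the PR directly, such as Poisson regression with a log link and robust variance. Logistic regression with case duplication and cluster-robust variance, or with standardised predictions, would serve equally if the step is stated. Use the same wording for the adjusted models.
2. State that the interaction terms in both effect-modification aims (fitness by IAP, high-risk delivery by MVPA) are tested on the PR scale. Name the link in the Table 2 footnote.
3. Reword the fitness by IAP hypothesis from odds to prevalence.

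An additive-scale estimate beside the PR-scale test is optional. If the full protocol or analysis plan already names the PR-yielding step, the article need only match it.

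The cost is wording only, with no change to data collection or sample size. A log-link Poisson model can give fitted prevalences above 1 at extreme covariate values, so that check should be added.
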